## 1. Introduction

Diabetes mellitus (DM) is a major public health problem, with over 400 million adults diagnosed worldwide. The prevalence of the disease is increasing, and, by 2040, the International Diabetes Federation (IDF) estimates that approximately 700 million adults will be diagnosed with DM [1]. Clinical and epidemiological data indicate that patients with DM are at high risk for adverse outcomes, such as myocardial infarction and other atherosclerosis-related cardiovascular (CV) events [2], as well as renal failure. Heart failure (HF) is a major contributor to cardiovascular (CV) morbidity and mortality in DM, with prevalence in type II DM (T2DM) up to 28% [3]. Risk factors for HF in DM include established CV disease, the presence of CV risk factors and chronic kidney disease [4,5]. Importantly, patients with both HF and DM have a higher risk of CV death or HF hospitalization than patients with either one of the diseases alone [6].

As per the ACC/AHA HF classification, patients with DM have, at least, stage A HF, i.e., are at risk for developing clinical HF. The distribution of DM patients in HF stages A/B/C was 48%, 36% and 16% in a study of patients of age ≥ 60 years with previously unrecognized HF [7]. Over a quarter of T2DM patients aged ≥60 years may have unrecognized clinical HF [8]. The risk of progression to symptomatic HF (stage C) from asymptomatic left ventricular diastolic dysfunction or systolic dysfunction (Stage B) is 8- and 2-fold higher than the respective risk of stage A [9]. The global longitudinal strain may independently predict incident HF among stage B patients [10,11]. Cardiac biomarkers, including high-sensitivity cardiac troponin T (hs-cTnT) and amino-terminal pro-B-type natriuretic peptide (NT-proBNP), can enhance the recognition of HF among at-risk individuals, including T2DM, when combined with traditional risk scores [12]. Recently, a biomarker risk score that included high-sensitivity troponin T, NT-proBNP, high-sensitivity C-reactive protein and left ventricular hypertrophy on electrocardiogram was shown to stratify HF risk in patients with dysglycemia (diabetes and pre-diabetes) and inform the allocation of HF prevention therapies in these patients [13].

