### 2.2. Patient Population

Approximately 300 consecutive eligible patients, managed in real-life clinical settings in Greece, will be recruited in 11 Cardiology Departments that are HF centers of excellence. Patients will be either self-referred or referred by primary or secondary care physicians (endocrinologists, diabetologists, internists, other) to Cardiology Departments. Patients aged between 40 and 80 years with T2DM diagnosed within 10 years prior to enrolment who are at high or very high CV risk are eligible to be included in the study. High or very high CV risk is defined according to 2019 guidelines on diabetes, pre-diabetes and CV diseases from the European Society of Cardiology. Briefly, very high CV risk is defined as having either established CVD (ischemic heart disease (IHD), cerebrovascular disease (CeDV), peripheral arterial disease (PAD)) or other target organ damage (proteinuria, left ventricular hypertrophy (LVH) or retinopathy), or at least three major risk factors (age, hypertension, dyslipidemia, smoking and obesity (body mass index, BMI ≥ 30 kg/m^2^). High CV risk is defined as age ≥ 50 years and presence of at least one additional major risk factor. Recruitment will last up to 27 months. Each participating patient will be followed for up to 24 months or until death, withdrawal of consent or physician’s decision for patient withdrawal, whichever occurs earlier. Main exclusion criteria are diagnosis of T1DM, prior history of HF or treatment with SGLT2 inhibitor at the time of study enrolment because of the effect of this drug class to reduce new-onset HF in patients with T2DM. Detailed inclusion and exclusion criteria are listed in the Supplementary Materials.

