### 2.5. Study Objectives

The primary outcomes of the study are as follows: the proportion of patients diagnosed with symptomatic HF (Stage C) at enrolment in the overall study population, and the proportions of patients with HF stages A, B and C at enrolment, in the overall study population and based on NYHA functional classification. Select secondary outcomes include the following: the proportion of patients having progressed to higher HF stage at 2 years post-enrolment in the overall study population and in the subpopulations with HF stages A, B and C at enrolment; person-time incidence rate of symptomatic HF (stages C or D) defined as number of patients diagnosed with symptomatic HF per patient-years of observation since enrolment, in the study subpopulation with preclinical HF (stages A and B) at enrolment; proportions of patients with HF with reduced (HFrEF), mildly reduced (HFmrEF) and preserved left ventricular ejection fraction (HFpEF), overall and in the subpopulations with HF stages B and C at enrolment; change in the KCCQ-12 overall summary score and domain scores from enrolment to 6 and 24 months post-enrolment in the study subpopulation diagnosed with symptomatic HF (stage C) at enrolment; and person-time incidence rate of inpatient hospitalizations, emergency room attendances, admissions to an outpatient facility, visits at office-based physicians, home visits by physicians as well as medical procedures/interventions/diagnostic testing utilization for HF- and CV-related causes, in the overall study population and in the subpopulations with HF stages A, B and C at enrolment. A complete list of the secondary and exploratory outcomes of the study is presented in the Supplementary Materials.

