### 2.6. Statistical Analysis

This study does not aim to confirm or reject any pre-defined hypotheses; therefore, statistical analysis will mainly be of descriptive and exploratory nature. Inferential statistics will be used for the estimation of the confidence intervals (CIs) of the primary and secondary outcomes (as applicable) as well as in the context of the exploratory outcome analyses. Continuous variables will be summarized using descriptive statistical measures (number of patients with available observations (n_pt_), number of missing observations (n_miss_), mean, standard deviation (SD), median, 25th and 75th percentiles, minimum (min) and maximum (max)), and categorical variables will be displayed using frequency tables (n_pt_, %). The normality of distribution of continuous variables will be examined using the Shapiro–Wilk test. Differences from baseline will be assessed using repeated measures analysis of variance (ANOVA). Concerning binomial proportions, the 95% CIs will be derived from Wald confidence limits for binomial proportions, while for incidence rates, the 95% Poisson CIs will be estimated. Time-to-event analysis will be conducted using the Kaplan–Meier method.

The impact of patients’ characteristics on variables of interest will be evaluated using binary or multinomial logistic regression models for nominal outcome variables. Cox proportional hazard regression models will be applied in order to examine the association of selected factors of interest with the time-to-event outcome variables. Multivariable regression models may be fitted, providing that the number of events/patients in each model is sufficient to allow for meaningful inferences. Missing covariates will be addressed within the appropriate imputation method.

All analyses will be performed in the set of all eligible enrolled patients and in the subpopulations of interest. A comprehensive and detailed description of the statistical methodology for the purposes of the analysis along with imputation methods for missing dates, missing covariates and censoring rules for Kaplan–Meier estimations will be provided in the statistical analysis plan (SAP). All statistical tests will be two-sided, and *p* values will be reported.

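### Wald limits are fixed for every proportion: adequate for the primary stage C proportion, but they under-cover sparse proportions in the stage subgroups

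*Protocol article*

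**What the plan says.** Section 2.6 (Statistical Analysis) names one interval method for all proportions: "the 95% CIs will be derived from Wald confidence limits for binomial proportions". It states no exception for small groups or low counts. The same section says that the study tests no pre-defined hypothesis, and that inferential statistics serve to give confidence intervals for the primary and secondary outcomes and to support the exploratory analyses.

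Section 2.5 (Study Objectives) lists the proportions concerned. The primary ones use the whole cohort: stage C at enrolment, and the distribution over stages A, B and C. Among the secondary ones is "the proportion of patients having progressed to higher HF stage at 2 years post-enrolment in the overall study population", which is also wanted separately within stages A, B and C. The split into reduced, mildly reduced and preserved ejection fraction is wanted overall and within stages B and C.

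On size, Section 2.2 says: "Approximately 300 consecutive eligible patients, managed in real-life clinical settings in Greece, will be recruited in 11 Cardiology Departments". The article gives no precision target and no expected stage distribution for this cohort. The Introduction cites two sets of results from other studies that can serve as scenarios. One is the split 48/36/16% over stages A/B/C in patients aged 60 or over. The other is heart failure prevalence in type 2 diabetes, "with prevalence in type II DM (T2DM) up to 28" per cent, together with a statement that more than a quarter of those aged 60 or over may have unrecognised clinical heart failure.

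**The concern.** The Wald interval takes its standard error from the observed proportion. When few events are expected, that estimate is often too small, and with no events it is zero. The interval is also symmetric, so with one, two or three events its lower limit falls below zero. These faults depend on the expected number of events, so they can appear in the stage subgroups even if the whole-cohort result is sound.

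The intervals matter more here than in a trial with a formal test, because for the primary and secondary proportions they are the only statement of uncertainty. A reader who sees 0% to 0% for progression within a subgroup of a few dozen patients would take it as certainty. The article names the method outright, so an analysis plan that follows it would inherit the problem.

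**Working it through.** The article has no precision figure to reproduce, so the check is the coverage of the stated method.

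**Inputs**
- Cohort size n = 300 and 11 centres (Section 2.2).
- Confidence level 95%, so z = 1.96 (Section 2.6).
- Stage sizes as scenarios (Introduction): 0.48 × 300 = 144 in A, 0.36 × 300 = 108 in B, 0.16 × 300 = 48 in C. As an alternative, one quarter with clinical heart failure gives 0.25 × 300 = 75 in C.
- True proportions within subgroups: not in the article; a range from 1% to 50% is assumed.

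**Formulas** (p̂ = x/n)
- Wald: p̂ ± z√(p̂(1−p̂)/n).
- Wilson: [p̂ + z²/2n ± z√(p̂(1−p̂)/n + z²/4n²)] / (1 + z²/n).
- Exact coverage at true p: the sum of the binomial(n, p) probabilities of all x whose interval contains p.

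**Step 1: whole-cohort proportions, n = 300**

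| True p | Wald coverage | Wilson coverage |
|---|---|---|
| 16% | 94.9% | 95.2% |
| 28% | 95.2% | 95.4% |
| 36% | 94.6% | 95.3% |
| 48% | 94.4% | 94.4% |

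For 48/300 the Wald limits are 11.9% to 20.2% and the Wilson limits 12.3% to 20.6%. The Wald form is adequate for the primary outcomes.

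**Step 2: stage subgroups**

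| n (scenario) | True p | Wald coverage | Wilson coverage |
|---|---|---|---|
| 48 (C) | 2% | 62.0% | 92.9% |
| 48 (C) | 4% | 85.6% | 95.8% |
| 48 (C) | 10% | 86.4% | 94.7% |
| 48 (C) | 20% | 92.9% | 95.4% |
| 48 (C) | 50% | 94.1% | 94.1% |
| 75 (C, alternative) | 2% | 78.0% | 93.6% |
| 108 (B) | 1% | 66.1% | 97.6% |
| 108 (B) | 5% | 90.3% | 95.2% |
| 144 (A) | 1% | 76.4% | 94.3% |
| 144 (A) | 5% | 92.7% | 94.8% |

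The shortfall at n = 48 and p = 2% is nearly all due to samples without events: 0.98⁴⁸ = 37.9%, and each such sample yields a zero-width interval that misses 2%. The Wilson interval is not perfect either: at n = 48 and p = 1% it covers 91.7%, but Wald covers 38.3% there.

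**Step 3: limits that would be printed at n = 48**

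| Events | Wald | Wilson | Clopper-Pearson |
|---|---|---|---|
| 0 | 0% to 0% | 0% to 7.4% | 0% to 7.4% |
| 1 | −2.0% to 6.1% | 0.4% to 10.9% | 0.05% to 11.1% |
| 2 | −1.5% to 9.8% | 1.2% to 14.0% | 0.5% to 14.3% |
| 3 | −0.6% to 13.1% | 2.2% to 16.8% | 1.3% to 17.2% |

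**Step 4: centre, conditional only**

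A plain binomial limit takes no account of centre. With a mean of 300/11 = 27.3 patients per centre, the design effect is 1 + 26.3 × ICC. The intracluster correlation (ICC) is not in the article. At assumed values of 0, 0.01, 0.02 and 0.05 the design effect is 1, 1.26, 1.53 and 2.31. The Wald coverage of a 16% primary proportion is 94.9% at zero (exact) and 91.8%, 88.5% and 80.0% at the other values (beta-binomial simulation, 40,000 runs). These results follow from the assumed ICC and show nothing about the true one.

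**The case against.** The strongest reply has four parts.

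- **The main result is sound and the study is descriptive.** This stands. A reader might infer from a criticism of the Wald interval that the primary intervals are wrong. They are not: Step 1 shows coverage of 94.4% to 95.2% across the stage shares and the prevalence that the article cites.
- **Subgroup sizes and event rates are assumed.** This stands too. The 48/36/16% split comes from an older, different population and is not a design assumption, and the article gives no expected rate of progression or of any phenotype. The alternative of 75 patients softens the figure without removing the problem. It would be too much to say that most subgroup intervals fail: at n = 48 and p = 20% or more the loss is about two points or less.
- **Detail is left to the analysis plan.** This does not answer the point, because the article does not leave the interval method open; it names it.
- **Centre may be handled there.** This stands. A reader might infer from "will be recruited in 11 Cardiology Departments that are HF centers of excellence" that the intervals are too narrow because patients cluster. The article gives no ICC, does not say that referral patterns differ between centres, and does not say how the analysis will treat centre. That is a possible risk, not a demonstrated error.

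**Conclusion.** The point holds in a limited form. Fixing Wald limits for every proportion is a poor choice for sparse proportions in the stage subgroups, and harmless for the primary stage C proportion. If stage C has about 48 patients, a nominal 95% interval would cover 62% of the time at a true 2% and 86% at 4% or 10%. With 75 patients it would cover 78% at 2%. Zero-width intervals and negative lower limits would appear whenever a subgroup has no events, or one to three.

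The size rests on two assumptions: the stage split borrowed from a cited study, and true subgroup proportions of about 10% or below. Progression within stage C is the most plausible such case; ejection-fraction phenotypes may or may not be. The documents do not support a claim against the primary intervals, nor a firm claim about clustering by centre.

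**What to change.** In Section 2.6, and in the analysis plan, replace the Wald limits by Wilson limits (or Clopper-Pearson, if coverage of at least 95% is wanted) for all proportions, primary and secondary. One rule for all is simpler than a threshold for switching, and it changes the primary interval by less than half a point at each end (Step 1).

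The cost is a change of one sentence and a standard software option. Intervals for sparse counts become asymmetric and somewhat wider: for 1/48 the width goes from 8.1 to 10.5 points. Clopper-Pearson is wider still in most sparse cells.

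Optionally, add a sensitivity interval for the primary proportion that allows for centre, for example a centre-robust standard error with t quantiles on 10 degrees of freedom. In the simulation of Step 4 it covered 93.9% to 94.5% at 16% for an ICC of 0.01 to 0.05. It is more work than the first change. It should stay secondary, because the ICC is unknown. A random-intercept logistic model is less suitable, since without averaging over centres it estimates a different quantity from the cohort proportion.

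### One Poisson CI rule covers all incidence rates; for the healthcare-use rates, where a patient can have several contacts, it will tend to give intervals that are too narrow, severely so only for frequent contacts

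*Protocol article*

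**What the plan says.** Section 2.6 (Statistical Analysis) plans inference for the "estimation of the confidence intervals (CIs) of the primary and secondary outcomes (as applicable") and, after naming a method for binomial proportions, fixes the method for rates: "while for incidence rates, the 95% Poisson CIs will be estimated". It does not separate kinds of rate and mentions no overdispersion or patient-level variance. Detailed methodology is referred to an SAP.

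Section 2.5 (Study Objectives) lists two kinds of person-time rate among the secondary outcomes:

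- The symptomatic-HF rate in patients with stage A or B at enrolment, "defined as number of patients diagnosed with symptomatic HF per patient-years of observation since enrolment". Its numerator is patients.
- The healthcare-use rates for HF- and CV-related causes, overall and by stage: "person-time incidence rate of inpatient hospitalizations, emergency room attendances, admissions to an outpatient facility, visits at office-based physicians, home visits by physicians", followed by procedures, interventions and diagnostic testing. Their numerator is not defined.

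Section 2.2 gives the scale: "Approximately 300 consecutive eligible patients, managed in real-life clinical settings in Greece". On follow-up it says: "Each participating patient will be followed for up to 24 months or until death".

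**The concern.** A Poisson interval for a rate takes the variance of the total count to equal its mean. That is reasonable when each patient contributes at most one event. When a patient can contribute many, it requires all patients to share the same underlying rate and events within a patient to be independent. If patients differ in how much care they use, the variance exceeds the mean and the interval is too short.

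The article gives reason to expect such differences. The overall cohort pools HF stages A, B and C. Section 2.2 admits patients ranging from those with risk factors only to those with established cardiovascular disease. Section 2.3 leaves visit frequency to the hospital investigators. Section 1 names the measurement of resource use by HF stage as an aim, which presumes that use may differ by stage.

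At stake is the stated precision of the resource-use estimates. In a descriptive study these intervals are part of the product, and readers will probably compare the stage-specific ones by eye.

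**Working it through.** The article gives no event rate, dispersion or interval width for these outcomes, so there is no figure of its own to reproduce. The check asks how far a Poisson interval falls short over a range of assumed values.

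**Inputs from the article.** About 300 patients; up to 24 months each, so at most 300 × 2 = 600 patient-years. To size a stage C subgroup, the introduction cites an earlier study: "The distribution of DM patients in HF stages A/B/C was 48%, 36% and 16"%. Taking 16% gives 0.16 × 300 = 48 patients. That study enrolled patients aged 60 or over, whereas this one enrols ages 40 to 80, so 48 is only illustrative.

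**Assumptions.** Full 2-year follow-up; negative-binomial counts with mean m = rate × 2 and variance m + αm², where α is the dispersion; exact Poisson limits on the total count; all events counted. Rates from 0.05 to 4 per patient-year and α from 0.5 to 4 are chosen to show a range.

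**Formulas.**

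- Variance relative to Poisson: (m + αm²)/m = 1 + αm.
- Needed width relative to the Poisson interval: √(1 + αm).
- Approximate coverage of the nominal 95% interval: 2Φ(1.96/√(1 + αm)) − 1.

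**Frequent contacts, worked.** Rate 2 per patient-year, so m = 4; α = 1.

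- Variance per patient is 4 + 16 = 20, against 4 under Poisson. The ratio is 5 and √5 = 2.24.
- With 300 patients the expected total is 1,200 events in 600 patient-years. The Poisson SE of the rate is √1200/600 = 0.058. The true SE is √(300 × 20)/600 = 0.129.
- By normal approximation the Poisson interval is about 1.89 to 2.11, and the interval that allows for the heterogeneity is about 1.75 to 2.25.
- Approximate coverage is 2Φ(1.96/2.24) − 1 = 61.9%. Simulation gives 62.2%.

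**Rare events, worked.**

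- Rate 0.05, so m = 0.1; α = 0.5: √(1 + 0.05) = 1.02.
- Rate 0.1, so m = 0.2; α = 4: √(1 + 0.8) = 1.34.

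**Full range, 300 patients.** Each cell shows the needed width factor and the simulated coverage of the 95% Poisson interval (20,000 replicates).

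| Rate per patient-year | α = 0.5 | α = 1 | α = 2 | α = 4 |
|---|---|---|---|---|
| 0.05 | 1.02; 95.2% | 1.05; 94.4% | 1.10; 93.6% | 1.18; 91.4% |
| 0.1 | 1.05; 95.0% | 1.10; 94.2% | 1.18; 91.8% | 1.34; 87.8% |
| 0.3 | 1.14; 92.1% | 1.26; 89.1% | 1.48; 82.5% | 1.84; 71.6% |
| 2 | 1.73; 74.0% | 2.24; 62.2% | 3.00; 48.2% | 4.12; 37.2% |
| 4 | 2.24; 62.0% | 3.00; 48.6% | 4.12; 36.9% | 5.74; 26.8% |

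With no heterogeneity, coverage is 95% to 96%, so the shortfall comes from the heterogeneity alone.

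**Subgroup of 48.** The width factor does not depend on the number of patients. At rate 2, coverage falls from 75.7% (α = 0.5) to 37.7% (α = 4), much as with 300. At rate 0.05 it runs from 97.8% to 95.4%: nominal or conservative, because exact limits are wide when few events are expected (48 × 2 × 0.05 = 4.8).

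**The case against.** A reader might infer that every healthcare-use interval will be far too narrow, that differences between stages will be falsely declared, and that the plan cannot stand without repair. The documents do not support this.

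- Repeated counting is not stated. The only numerator section 2.5 defines is patients, for symptomatic HF. A first-event rate is possible, and the complete list of secondary and exploratory outcomes is in supplementary materials that are not shown. Still, counting all contacts is the natural reading, since a first-visit rate would not measure the burden of use that the introduction names as an aim.
- No rate or dispersion is given. Some listed contacts, such as HF or CV hospitalizations, may be rare in patients with no prior HF, and there the shortfall is slight to moderate. Severe under-coverage needs frequent contacts such as office visits or tests.
- Neither section 2.5 nor section 2.6 specifies a between-stage test or rate ratio for healthcare use, and section 2.6 disclaims pre-defined hypotheses. Comparison of intervals by eye remains a risk, but no planned conclusion rests on it.
- The primary outcomes are proportions with their own interval rule. They are untouched, as is the symptomatic-HF rate.
- The unseen SAP may define counting rules and variance adjustments. That lowers confidence that the final intervals will be wrong, but deferring detail does not withdraw a method that the article names without qualification.

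These points limit the size and weight of the concern. They do not remove it: the rule as written does not fit recurrent counts that vary between patients.

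**Conclusion.** The concern holds in a limited form. Applied as written, the Poisson rule will tend to make intervals for recurrent healthcare-use rates too narrow. Under the assumed range, the interval needs to be about 1.7 to 5.7 times as wide for contacts at 2 to 4 per patient-year, and only 1.02 to 1.34 times as wide for events at 0.05 to 0.1. All these sizes rest on assumed rates, assumed negative-binomial dispersion, full 2-year follow-up and the reading that all events are counted. Point estimates are unaffected, and only secondary, descriptive outcomes are involved. It is therefore a recommended correction for secondary outcomes, not a must-fix.

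**What to change.** In section 2.6 and the SAP:

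1. State that the numerator of each healthcare-use rate counts all events.
2. Keep Poisson intervals for once-per-patient events, such as incident symptomatic HF and death.
3. For recurrent-event rates, overall and by stage, use either a Poisson rate with patient-level robust (sandwich) or bootstrap variance, or a negative-binomial model with a log person-time offset. Name one of these in advance.

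This takes a sentence or two and no new data, provided contacts are recorded per patient with dates or counts. The cost is wider reported intervals where use is heterogeneous; where it is not, they will be close to the Poisson ones. For rare events in a small stage group (about 5 expected events in the example above), a patient-level variance rests on very few patients, so the event count and the number of patients with an event should be shown beside the interval.
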